### **1.9 Data Safety Monitoring Committee**

No Data Safety Monitoring Committee is foreseen for this phase 2 clinical trial.

## 2. ETHICAL AND REGULATORY ASPECTS

### 2.1 Study registration

This clinical trial will be registered in the SNCTP and in the ClinicalTrials.gov registry prior to the conduct of the trial [1].

### 2.2 Categorisation of study

The category of this clinical trial is B, since the medicinal product is authorised in Switzerland but in a different indication (thrombosis prophylaxis in orthopaedic surgery) [2, 3].

### 2.3 Competent Ethics Committee (CEC)

This clinical trial will be submitted for approval to the Competent Ethics Committee of the Kanton Bern (KEK). In case other national or international centres will be opened, the trial will be submitted for approval to the respective CEC as requested. Any study related procedure will be conducted only after written approval from the respective CEC will be available.

### 2.4 Competent Authorities (CA)

This clinical trial will be submitted for approval to the Competent Authority (Swissmedic). Any study related procedure will be conducted only after written approval from Swissmedic will be available. In case international centres will be included, the trial will be submitted for approval to the respective Competent Authorities as requested.

### 2.5 Ethical Conduct of the Study

The study will be carried out in accordance with the protocol and with principles enunciated in the current version of the Declaration of Helsinki, the guidelines of Good Clinical Practice (GCP) issued by ICH, the Swiss Law and Swiss regulatory authority's requirements and any other applicable international law, if applicable. The CEC and regulatory authorities will receive annual safety and interim reports and be informed about study stop/end in agreement with local requirements [2, 4-6].

### 2.6 Declaration of interest

This clinical trial is supported by a unrestricted financial grant provided by Bayer Pharma AG and Janssen Pharmaceuticals, Inc. Sponsor and investigators declared no other conflict of interest.

### 2.7 Patient Information and Informed Consent

The investigators will explain to each participant the nature of the study, its purpose, the procedures involved, the expected duration, the potential risks and benefits and any discomfort it may entail. Each participant will be informed that the participation in the study is voluntary and that he/she may withdraw from the study at any time and that withdrawal of consent will not affect his/her subsequent medical assistance and treatment.

The participant must be informed that his/her medical records may be examined by authorised individuals other than their treating physician.

All participants of the study will be provided a participant information sheet and a consent form describing the study and providing sufficient information for participants to make an informed decision about their participation in the study.

The patient information sheet and the consent form will be submitted to the CEC and to the competent authority (as applicable) to be reviewed and approved. The formal consent of a participant, using the approved consent form, must be obtained before the participant is submitted to any study procedure.

The participant should read and consider the statement before signing and dating the informed consent form, and should be given a copy of the signed document. The consent form must also be signed and dated by the investigator (or his designee) and it will be retained as part of the study records.

In case that there is relevant new information regarding the investigational trial product or any relevant adaptation of trial procedures, an amendment of the trial protocol will be submitted to the independent ethics committee and patients will have to re-consent.

### 2.8 Participant privacy and confidentiality

The investigator affirms and upholds the principle of the participant's right to privacy and that he shall comply with applicable privacy laws. Especially, anonymity of the participants shall be guaranteed when presenting

the data at scientific meetings or publishing them in scientific journals.

Individual subject medical information obtained as a result of this study is considered confidential and disclosure to third parties is prohibited. Subject confidentiality will be further ensured by utilising subject identification code numbers to correspond to treatment data in the computer files.

For data verification purposes, authorised representatives of the Sponsor, a CA (e.g. Swissmedic), or a CEC may require direct access to parts of the medical records relevant to the study, including participants' medical history.

## **2.9 Early termination of the study**

The Sponsor may terminate the study prematurely according to certain circumstances, for example:

- insufficient participant recruitment,
- when the safety of the participants is doubtful or at risk, respectively,
- alterations in accepted clinical practice that make the continuation of a clinical trial unwise, early evidence of benefit or harm of the experimental intervention.

## **2.10 Protocol amendments**

Substantial amendments are only implemented after approval of the CEC and CA respectively.

Under emergency circumstances, deviations from the protocol to protect the rights, safety and well-being of human subjects may proceed without prior approval of the sponsor and the CEC/CA. Such deviations shall be documented and reported to the sponsor and the CEC/CA as soon as possible.

All non-substantial amendments are communicated to the CA as soon as possible if applicable and to the CEC within the Annual Safety Report (ASR).

# **3. BACKGROUND AND RATIONALE**

## **3.1 Background and Rationale**

The prevalence of obesity and morbid obesity is increasing worldwide and is becoming an increasing medical and socioeconomic burden [7]. The rise in morbid obesity led to a significant increase in bariatric surgery driven by the advancements in surgical techniques and use of laparoscopy [8]. Despite key improvements in the perioperative management, there are potential risks, among them venous thromboembolism (VTE) [9]. The incidence of symptomatic deep vein thrombosis (DVT) ranges from 1% - 3%, and the incidence of pulmonary embolism (PE) from 0.3% - 2% [10-12]. The incidence of clinically inapparent venous thromboembolism in bariatric patients is not known, but might be considerably higher, taking into account data reported by Vedovati et al. in patients undergoing laparoscopic surgery for colorectal cancer [13].

Although the overall incidence is low, VTE remains a leading cause of morbidity and mortality after bariatric surgery [14, 15]. The American Society for Metabolic and Bariatric Surgery (ASMBS) and the American College of Chest Physicians have recommended in addition to mechanical prophylaxis some methods of VTE prophylaxis with lower extremity compression and some form of pharmacoprophylaxis [16]. However, strategies of adjusted-dose heparins and post discharge anticoagulant prophylaxis of low-molecular-weight heparins as standard treatment were not clearly defined. In addition, there is a lack of randomized controlled trials addressing this topic. Since most post-discharge VTE events occur within the first 28 days after bariatric surgery and the incidence rises within this time-period an extended duration of thromboprophylaxis after hospital discharge should be investigated [17]. Analysis of postdischarge heparin prophylaxis for bariatric surgery is limited to date, but results from Raftopoulos et al. are promising and showed that the 28-day VTE rate was significantly higher in the group that only received in-hospital prophylaxis with enoxaparin compared to the extended pharmacoprophylaxis group [18].

In 2016, the Scientific and Standardization Committee (SSC) of the International Society on Thrombosis and Haemostasis (ISTH) published a guidance document that included a suggestion to not use DOACs in patients with a BMI greater than 40 kg/m^2 or weight exceeding 120 kg due to limited clinical data and concerns regarding the potential effects of body weight extremes on the PK and PD of these agents [19]. So far, only limited data are available on the use of direct oral anticoagulants (DOACs) in morbidly obese patients and patients who have undergone bariatric surgery.

Rivaroxaban has been extensively studied in a variety of clinical indications, was generally well tolerated and demonstrated a predictable, dose-dependent pharmacologic profile up to 24 hours after single dose

administration. The anticoagulant has a high oral bioavailability (80-100%) irrespective of food intake, a rapid onset of action and the maximum plasma level is achieved two to four hours after oral administration [20, 21]. One major advantage of DOACs is the fact that there is no need to modify the dosage for extreme body weights up to 150 kg [22, 23].

Nevertheless, in these patients anatomic and physiologic changes to the digestive system can influence drug pharmacokinetics, the extent of which may differ over the short and long term. Based on theoretical pharmacological concepts, absorption in patients with a Roux-en-Y-gastric bypass or a sleeve gastrectomy could be impaired due to the fact that parts of the upper GI tract are bypassed or removed, since rivaroxaban is mostly absorbed in the upper gastrointestinal tract including stomach and the small intestine.

However, there was no significant change of pharmacodynamics and pharmacokinetics in our phase I clinical trial assessing single doses of 10 mg rivaroxaban prior to and after bariatric surgery (see also below at 3.4) [24].

The aim of this study is to investigate the safety and efficacy of rivaroxaban in obese patients undergoing bariatric surgery. Rivaroxaban as an oral anticoagulant could be an attractive option for thromboprophylaxis compared to subcutaneous standard treatment after bariatric surgery. Especially in high-risk patients where an extended duration of thromboprophylaxis after hospital discharge is recommended, an oral therapy would be desirable. The results of this trial will elucidate the clinical applicability of rivaroxaban in bariatric patients and will help to design larger phase III trials in this particular patient population with the final goal of a safe and efficient use of rivaroxaban in morbidly obese patients. Especially in high-risk patients, where an extended duration of thromboprophylaxis after hospital discharge is considered, an oral therapy would be attractive.

### **3.2 Investigational Product (treatment) and Indication**

Rivaroxaban (BAY 59-7939, Xarelto®) is an orally administered, direct Xa inhibitor and is used for the prevention and treatment of thromboembolic disorders. It is rapidly absorbed in the upper gastrointestinal tract. Rivaroxaban is generally well tolerated and demonstrates a predictable, dose-dependent pharmacology profile up to 24 hours after single dose also in obesity patients with no need for dose adjustment irrespective of age, weight and gender [22, 25].

### **3.3 Preclinical Evidence**

Non-clinical data reveal no special hazard for humans based on conventional studies on safety pharmacology, single dose toxicity, phototoxicity, genotoxicity, carcinogenic potential and juvenile toxicity.

Effects observed in repeat-dose toxicity studies were mainly due to the exaggerated pharmacodynamic activity of rivaroxaban. In rats, increased IgG and IgA plasma levels were seen at clinically relevant exposure levels.

In rats, no effects on male or female fertility were seen. Animal studies have shown reproductive toxicity related to the pharmacological mode of action of rivaroxaban (e.g. haemorrhagic complications).

Embryo-foetal toxicity (post-implantation loss, retarded/progressed ossification, hepatic multiple light coloured spots) and an increased incidence of common malformations as well as placental changes were observed at clinically relevant plasma concentrations. The cause of the embryo-foetal toxicity is not known. In the pre- and postnatal study in rats, reduced viability of the offspring was observed at doses that were toxic to the dams [20].

### **3.4 Clinical Evidence to Date**

In multiple Phase I and II studies Rivaroxaban was safe and demonstrated predictable, dose-dependent pharmacokinetics and pharmacodynamics up to 24 hours after single dose application. Rivaroxaban (10 mg) has a high oral bioavailability (80-100%) irrespective of food intake, has a rapid onset of action and the maximum plasma level is achieved two to four hours after oral administration. The oral application of rivaroxaban is approved for the prevention of venous thromboembolism in patients after elective hip and knee surgery in Switzerland (Swissmedic) as well as in the European Union (EMA) and the USA (FDA). In a study by Kubitz et al., Rivaroxaban was well tolerated,  $C_{max}$  of rivaroxaban was unaffected in subjects >120 kg and the area under the curve (AUC) was unaffected by body weight and gender.

Absorption of rivaroxaban is dependent on the site of drug release in the GI tract. In a study looking at administration of the crushed tablet via a tube, a 29% and 56% decrease in AUC and  $C_{max}$  compared to an oral tablet was reported when rivaroxaban granulate was released in the proximal small intestine [26]. It is therefore anticipated that the Roux-en-Y gastric bypass surgery will have some effect on the absorption of rivaroxaban.

However, our phase I clinical investigation showed that the pharmacokinetics and pharmacodynamics of a single 10 mg dose of rivaroxaban did not significantly change after bariatric surgery compared to the investigation in the same patients prior to the surgical intervention [24]. In our clinical trial we could furthermore demonstrate that single doses of rivaroxaban were associated with predictable pharmacodynamics and were well tolerated

in obese patients prior to and 3 days after bariatric surgery [27]. Our findings are in line with a case study reported by Mahlmann et al. where the absorption of rivaroxaban was immediate and not significantly impaired by bariatric surgery of the upper GI tract [28].

### **3.5 Dose Rationale**

Rivaroxaban is approved for the prophylaxis of venous thrombosis after major orthopaedic surgery. In this specific indication a dose of 10 mg rivaroxaban QD is used [29]. In analogy to the approved dose and indication, a dose of 10 mg rivaroxaban QD will be used in this phase 2 clinical trial addressing safety and efficacy of Rivaroxaban in post-bariatric surgery patients.

### **3.6 Explanation for choice of comparator (or placebo)**

No comparator is used in this early clinical trial addressing safety and efficacy of VTE with rivaroxaban in post-bariatric surgery patients.

### **3.7 Risks / Benefits**

Since rivaroxaban is already approved in different indications, there is no general concern regarding its risk profile. The major risk is associated with bleeding. On the other side, ischemic events can be prevented with successful thromboembolic prophylaxis.

Bariatric surgery is performed according to clinical routine. Patients receive the first postoperative dose of rivaroxaban (10 mg) on the first postoperative day. Data of our previous single dose PK/PD study have shown PK/PD effects comparable to non-bariatric postsurgical patients without evidence of a bleeding or a thromboembolic adverse event.

Currently, there is no common recommendation available regarding the duration of VTE prophylaxis in post-bariatric patients. The benefit of this trial will be the generation of new safety and efficacy data regarding the duration of VTE prophylaxis in this specific patient population.

Prophylaxis with rivaroxaban had a significantly higher efficacy in VTE prophylaxis as compared with enoxaparin after hip and knee replacement surgery as was shown in the large RECORD clinical trial programme with similar rates of bleeding [29-32].

With this clinical phase 2 trial that is based on our previous phase 1 PK/PD trial [24], safety and feasibility of an anticoagulation with rivaroxaban will be investigated in bariatric patients. Since to date there is no phase 2 data available for bariatric patients, this trial will be the next step needed to finally introduce a prophylactic anticoagulation with rivaroxaban in bariatric patients.

In case of confirmed safety and efficacy, oral anticoagulation with rivaroxaban will be beneficial for bariatric patients due to the facilitated application in form of tablets compared to daily subcutaneous injections of low-molecular weight heparins (LMWH) after surgery.

Based on the data of our phase 1 PK/PD trial [24] as well as of the available evidence from multiple trials in similar orthopaedic indications [29-32], the risk of the anticoagulation with the investigational product is similar to the standard of care application of LMWH.

With the methodology used in this study (details regarding the sample size calculation see at 11.2), new generalizable information will be generated for both study arms.

The most common adverse reactions with Xarelto® are bleeding complications. To minimize the risk for bleeding event, patients with an a priori higher risk for bleeding are excluded from this clinical trial.

The primary safety endpoint will be major bleeding. All adverse events will be collected and processed according to international guidelines and national legislation. Conduct of this clinical trial will be monitored by an independent third party.

Embryo-foetal toxicity (post-implantation loss, retarded/progressed ossification, hepatic multiple light coloured spots) and an increased incidence of common malformations as well as placental changes were observed at clinically relevant plasma concentrations. Therefore, use of a double barrier contraception method during the study is mandatory to minimize the risk for embryo-foetal toxicity.

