# 7. STUDY POPULATION

## 7.1 Eligibility criteria

Participants fulfilling all of the following inclusion criteria are eligible for the study:

- Patient with scheduled elective bariatric surgery or “redo”/revisional surgery after bariatric interventions
  - Roux-en-Y gastric bypass surgery (RYGB) or sleeve gastrectomy (SG)
  - Conversion from SG to RYGB
  - Conversion from gastric banding to SG or RYGB
  - Revision of gastric pouch or gastrojejunal anastomosis
  - Revision of jejuno-jejunostomy
- Patient aged 18 years or older
- BMI  $\geq 35$  kg/m^2
- Women of child-bearing age: Willingness of using a double barrier contraception method during the study period (up to 4 weeks after end of trial)
- Written, informed consent

The presence of any one of the following exclusion criteria will lead to exclusion of the participant:

- DVT and/or PE in the patient history
- Myocardial infarction, transient ischemic attack or stroke within 6 months of study entry
- Active pathological bleeding
- Uncontrolled hypertension
- Severely impaired hepatic function (cirrhotic patients with Child B or C) or renal function (creatinine clearance <30 mL per min)
- Concomitant treatment with strong CYP3A4 inhibitors (e.g., ketoconazole, itraconazole, lopinavir, ritonavir, indinavir).
- Concomitant treatment with a P-glycoprotein inhibitor and weak or moderate CYP3A4 inhibitor (e.g., erythromycin, azithromycin, diltiazem, verapamil, quinidine, ranolazine, dronedarone, amiodarone, felodipine).
- Concomitant treatment with P-glycoprotein inducers and strong CYP3A4 inducers (e.g. carbamazepine, phenytoin, rifampin).
- Therapy with any other drugs that might affect the study outcome, including anticoagulants, aspirin or other antiplatelet agents, Factor Xa inhibitors other than the study medication, or any other drug affecting coagulation
- Positive pregnancy test, pregnancy or nursing women
- Congenital or acquired bleeding disorder
- Known intolerance of the study medication rivaroxaban

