| Medical history                                                                       | X          |         |               |    |    |     |     |      |      |       |      |       | x                                                   |   |     |     |     |      |      |     |     |     |     |
| Concomitant medication                                                                | x          |         |               |    |    |     |     |      |      |       |      |       | x                                                   |   |     |     |     |      |      |     |     |     |     |
| Demographics                                                                          | x          |         |               |    |    |     |     |      |      |       |      |       |                                                     |   |     |     |     |      |      |     |     |     |     |
| Physical exam incl. weight and height                                                 | x          |         |               |    |    |     |     |      |      |       |      |       | x                                                   |   |     |     |     |      |      |     |     |     |     |
| Inclusion/Exclusion-criteria                                                          | x          |         |               |    |    |     |     |      |      |       |      |       |                                                     |   |     |     |     |      |      |     |     |     |     |
| Coagulation/hemostasis parameters (INR, Platelets)                                    | x          |         |               |    |    |     |     |      |      |       |      |       |                                                     |   |     |     |     |      |      |     |     |     |     |
| Liver and kidney function                                                             | x          |         |               |    |    |     |     |      |      |       |      |       |                                                     |   |     |     |     |      |      |     |     |     |     |
| Beta-HCG                                                                              | x          |         |               |    |    |     |     |      |      |       |      |       |                                                     |   |     |     |     |      |      |     |     |     |     |

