### **9.4 Procedures at each visit**

#### **9.4.1 Study independent preoperative assessments**

Patients who qualify for the study will undergo preoperative work-up according to routine clinical practice. These clinical preoperative investigations are performed to elucidate the causes of obesity and to screen for obesity-related co-morbidities with special attention to those factors that could affect the outcome of bariatric surgery.

This work-up includes the following procedures:

Comprehensive medical history, psycho social history, physical examination and clinical chemistry, hematology and coagulation testing to assess surgical risk according to the SMOB guidelines. Routine laboratory evaluation consists of the following parameters: sodium, potassium, calcium, phosphate, magnesium, glucose, creatinine, uric acid, albumin, transferrin, lipid profile, vitamin

B12, folic acid, HbA1c, TSH, fT3, fT4, cortisol, estradiol, LH, FSH, INR, differential blood.

In addition, following assessments are performed:

Gastrointestinal evaluation with an upper endoscopy incl. Helicobacter pylori testing to screen for gastrointestinal haemorrhage or ulcers. Cardiopulmonary risk assessment with sleep apnea screening by a cardiologist. Upper gastrointestinal image series. Abdominal ultrasound in case of symptomatic biliary disease or elevated liver function tests. Endocrine evaluation with ultrasound of the thyroid gland. Clinical nutrition evaluation. Psychosocial-behavioral evaluation by a psychologist [40, 41].

All these assessments are performed as part of the standard of care work-up.

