### **9.4.4 Start of treatment visit V1 (day 1)**

At V1, inclusion and exclusion parameters will be assessed and patient will be included if all inclusion criteria are met and none of the exclusion criteria is met. Subsequently, patient will be randomized to one of the two treatment arms. Study treatment with rivaroxaban will be started. In case patient is not able to take peroral medication at that point of time according to medical reasons, treatment with LMWH will continue until peroral medication can be provided. Collection of safety data (AE and SAE related data). D-Dimers are sampled and analysed in the subgroup of patients.

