#### Contraindications:

Hypersensitivity to the active substance or any of the excipients; active clinically significant bleeding; lesion or condition if considered a significant risk for major bleeding; concomitant treatment with any other anticoagulants except under the circumstances of switching therapy to or from rivaroxaban or when unfractionated heparin is given at doses necessary to maintain an open central venous or arterial catheter; hepatic disease associated with coagulopathy and clinically relevant bleeding risk including cirrhotic patients with Child Pugh B and C; pregnancy and breast feeding.

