#### Warnings and Precautions:

Clinical surveillance in line with anticoagulation practice is recommended throughout treatment. Xarelto should be discontinued if severe haemorrhage occurs. Increasing age may increase haemorrhagic risk. *Not recommended:* in patients with severe renal impairment (creatinine clearance  $<15$  ml/min); in patients receiving concomitant systemic treatment with strong concurrent CYP3A4- and P-gp-inhibitors, i.e.azole-antimycotics or HIV protease inhibitors; in patients with increased bleeding risk; in patients receiving concomitant treatment with strong CYP3A4 inducers unless the patient is closely observed for signs and symptoms of thrombosis; *not recommended due to lack of data:* in patients below 18 years of age, in patients concomitantly treated with dronedarone. 10 mg add: in patients undergoing hip fracture surgery; 15 mg / 20 mg add: in patients with prosthetic heart valves, in patients with **PE** who are haemodynamically unstable or may receive thrombolysis or pulmonary embolectomy. *Use with caution:* in conditions with increased risk of haemorrhage; in patients with severe renal impairment (creatinine clearance 15 - 29 ml/min) or with renal impairment concomitantly receiving other medicinal products which increase rivaroxaban plasma concentrations; in patients treated concomitantly with medicinal products affecting haemostasis. 10 mg add: when neuraxial anaesthesia or spinal/epidural puncture is employed; 15 mg / 20 mg add: specific dose recommendations apply for patients with moderate to severe renal impairment and in case of

DVT/PE-patients only if the patient's assessed risk for bleeding outweighs the risk for recurrent DVT/PE. In patients at risk of ulcerative gastrointestinal disease prophylactic treatment may be considered. Although treatment with rivaroxaban does not require routine monitoring of exposure, rivaroxaban levels measured with a calibrated quantitative anti-Factor Xa assay may be useful in exceptional situations. Xarelto contains lactose.

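### The exclusion of patients at higher bleeding risk promised in section 3.7 is only partly carried into the entry criteria: one product-label contraindication has no counterpart

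*Protocol*

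**What the plan says.** Section 3.7 names bleeding as the main risk of the drug and gives a patient-selection measure against it: "patients with an a priori higher risk for bleeding are excluded from this clinical trial". The sentence has no qualifier and does not point to a list.

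Section 7.1 holds the operative list of 12 exclusions, and the synopsis carries the same 12. Those closest to the point are "Active pathological bleeding" and "Congenital or acquired bleeding disorder". Others cover uncontrolled hypertension, severe liver or kidney impairment, interacting drugs, and anticoagulant or antiplatelet therapy.

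Section 9.4.4 fixes how the list is used at V1, just before randomisation: "patient will be included if all inclusion criteria are met and none of the exclusion criteria is met".

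The product summary in Appendix 17.1 lists among its contraindications "lesion or condition if considered a significant risk for major bleeding". It is a separate item from active bleeding and from liver disease with coagulopathy. On ulcers, the warnings in the same appendix say: "In patients at risk of ulcerative gastrointestinal disease prophylactic treatment may be considered".

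Section 9.4.1 describes the routine preoperative work-up, which includes an "upper endoscopy incl. Helicobacter pylori testing to screen for gastrointestinal haemorrhage or ulcers".

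**The concern.** Because 9.4.4 decides entry on the list alone, the statement in 3.7 is only as true as 7.1 makes it. If 7.1 lacks a category of bleeding risk that the protocol's own appendix treats as a contraindication, a patient in that category can be randomised to 7 or 28 days of rivaroxaban while the protocol tells the ethics committee and the authority that such patients are kept out.

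The stake is patient safety and the accuracy of the risk statement, not statistical validity. Major bleeding is the primary safety endpoint (5.4) and the use is off-label (8.1.1). There is no data safety monitoring committee (1.9), no interim analysis (11.4.5) and no statistical stopping rule (11.3). In that setting the entry criteria carry much of the protection.

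**Working it through.** No calculation applies, because the plan states no figure on this point. The check is an item-by-item comparison.

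**Step 1. Contraindications in 17.1 against exclusions in 7.1**

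| Contraindication in 17.1 | Counterpart in 7.1 |
|---|---|
| Hypersensitivity | Known intolerance of rivaroxaban |
| Active significant bleeding | "Active pathological bleeding" |
| "lesion or condition if considered a significant risk for major bleeding" | None |
| Other anticoagulants | Exclusion of anticoagulants and other drugs acting on coagulation |
| Liver disease with coagulopathy, including Child-Pugh B and C | Child B or C cirrhosis, together with "Congenital or acquired bleeding disorder" |
| Pregnancy and breast feeding | Pregnancy or nursing |

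Result: 5 matched + 1 unmatched = 6.

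**Step 2. Could another exclusion fill the gap?** Of the 12 exclusions in 7.1, seven address bleeding risk:

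1. active bleeding;
2. uncontrolled hypertension;
3. liver or kidney impairment;
4. strong CYP3A4 inhibitors;
5. P-glycoprotein inhibitors combined with weak or moderate CYP3A4 inhibition;
6. drugs affecting coagulation;
7. bleeding disorder.

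The count is eight if infarction, transient ischaemic attack or stroke within 6 months is included.

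- The active-bleeding criterion does not cover a lesion that is not bleeding. The appendix itself keeps the two apart.
- A bleeding disorder is a defect of coagulation, not a structural lesion.
- Uncontrolled hypertension and organ impairment are particular conditions. They cover part of what the label item could include.
- No exclusion is phrased as a general or investigator-judged bleeding risk.

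So 0 of 12 cover a non-bleeding lesion or bleeding risk in general.

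**Step 3. The synopsis.** Its exclusion list has the same items and therefore the same gap.

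**Step 4. A concrete path through the plan.** The endoscopy in 9.4.1 looks for two things. A haemorrhage leads to an exclusion in 7.1; an ulcer leads to none. Under 9.4.4 a patient with a non-bleeding ulcer who meets the other criteria is included. The finding is available before randomisation, but no rule uses it.

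**The case against.** The best counter-argument is that 3.7 is a narrative summary, not an operational criterion. It does not say that every such patient is excluded, and with seven or eight of 12 exclusions aimed at bleeding, it fairly describes the list. Nothing in the protocol promises to mirror the label, which is appended only in abbreviated form and has a different surgical indication for the 10 mg dose. The contraindication depends on judgement, and an investigator who considers a lesion dangerous has it in the appendix and would not give the drug. Section 17.3 directs use according to the product information. Section 7.4.2 allows withdrawal for any relevant medical condition that makes continuation unreasonable, not only after a bleed. Patients are worked up for elective surgery, have INR and platelets checked at screening (9.2), and receive LMWH as standard care (9.4.3).

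Much of this stands as mitigation: it makes actual harm less likely and keeps the point minor. It does not close the gap. The direction in 17.3 is label text for the person administering the drug, and 7.4.2 governs leaving the study, not entering it. LMWH as standard care shows that some anticoagulation is accepted, but the synopsis gives it as a single dose, whereas rivaroxaban runs for 7 or 28 days. If 3.7 was meant only to summarise 7.1, it does not say so.

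One further objection is fair: the contraindication does not name ulcers. The ulcer is an illustration. Its relevance rests on the endoscopy screening for it in 9.4.1 and on the appendix raising prophylactic treatment for patients merely at risk of ulcerative disease. The missing criterion is a matter of text and does not depend on that example.

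**Conclusion.** The point holds. Section 3.7 claims more than 7.1 and the synopsis deliver: five of the six label contraindications are carried over, and the one for lesions or conditions with a significant major-bleeding risk is not. As written, a patient for whom the appended label contraindicates the drug can meet all entry criteria and be randomised.

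The consequence is small. Both arms have the same entry criteria, so the comparison between them is not biased, and sample size and analysis are untouched. How many patients would be affected is not in the document and is not estimated here. The conclusion assumes only that 9.4.4 is applied as worded and that the criteria in 7.1 are complete. Closing the gap is a worthwhile but optional improvement.

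**What to change.** Add one exclusion to 7.1 and to the synopsis, for example: *any lesion or condition, other than the expected fresh surgical site, that the investigator judges to carry a significant risk of major bleeding (e.g. current or recent gastrointestinal ulceration)*. The surgical-site exception is needed because every patient is one day after surgery at V1.

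The criterion would be judged at V1 from what is already collected: history, preoperative endoscopy, INR and platelets. Patients merely at risk of ulcer stay eligible, in line with the appendix, which for them mentions only possible prophylactic treatment.

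If patients with such lesions are meant to be eligible, narrow the sentence in 3.7 to the bleeding risks listed in 7.1 instead.

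The cost is one line in two places, by amendment, with no new test. A few otherwise eligible patients would be screened out. Because the criterion rests on judgement, centres may apply it somewhat differently; the example and the surgical-site exception limit that.
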